### Study aims

The specific aims of the study are:

1. To determine whether program content and process fidelity for Tier 1 (for all students) and Tier 2 (for at risk and high risk students) differ between schools receiving a higher level of support (Consultation plus Coaching, C + C) and schools receiving a lower level of support (Consultation, C) for program implementers.

2. To determine whether school climate, office discipline referrals, and participants’ diagnostic status, symptom and impairment severity, coping skills, and academic productivity differ between schools receiving different levels of support (C or C + C).

3. To assess changes in mental health disparities brought about by Tier 1 (perception of school climate, student suspension rates) and Tier 2 (proportion of students with unmet need), respectively.

4. To determine the incremental cost-effectiveness of SWPBIS C versus SWPBIS C + C.

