### Child outcome measures for at risk/high risk children

Children’s diagnostic status, mental health symptoms, coping skills and functional impairment will be assessed at pre- and post-participation in CPP and FRIENDS. All of the parent measures are available in Spanish. Diagnostic status will be assessed via a computerized parent-structured interview [79,104]. This instrument reports three levels of diagnostic severity for each disorder: Positive, Intermediate (at-risk), or Negative. Upon completion of the structured interview, the independent evaluator (IE) will assign interference scores to each positive diagnosis in order to determine primary and secondary diagnoses [80], based on a seven-point scale, with lower scores indicating less severity. Changes in coping skills will be assessed via a 34-item self-report questionnaire [105] that measures coping strategies (seeking social support, self-reliance/problem-solving, distancing, internalizing, and externalizing). The total score for this measure will be used in outcome analyses.

Changes in mental health symptoms (*e.g.*, aggression, conduct problems, anxiety, somatic symptoms) will be measured via parent [106], child [107,108] and teacher [106] multi-axial rating scales. Teachers will also provide changes in children’s grades and rate of academic productivity [109]. After all parent, child and teacher data are collected at pre- and post-, the IEs will complete a measure of functional impairment [110].

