The general analytical approach for testing our hypotheses will be the Laird and Ware mixed effects model [112] and the Generalized Estimating Equation (GEE) approaches [113,114]. Mixed effects and GEE are statistical approaches based on regression techniques for analyzing correlated data collected repeatedly from the same subject. The study design will allow us to examine the between- subjects effect related to the two levels of support, and a within-subjects effect corresponding to time points (five time points), as well as a type of support (C, C + C) by time interaction effect. These analyses will be conducted using SAS Proc Mixed, which utilizes the mixed effects models, and SAS Proc Genmod, which utilizes GEE [115]. Both the mixed effects model and GEE approaches allow estimation of fixed effect parameters such as time, and time by treatment interaction. If the interaction term is significant, it indicates that change in school climate and/or reduction in ODRs over time is significantly different between the two levels of support. If the interaction term is statistically not significant, the changes over time for the two primary outcomes will be presented by the time effect only, which represents both levels of support. The advantage of utilizing these methods is that all information available from each student is used, including variables with missing observations. In the proposed analyses, we will consider students measured within classes are correlated and will be nested within classes. Nested analysis will be chosen as part of Proc Mixed and Proc GEE, as such, the intraclass ‘intracluster’ correlation (ICC) will be part of the overall variance covariance matrix.

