Changes from pre- to post- implementation in diagnostic status, symptom severity and impairment level, coping skills and academic productivity during Implementation across all schools, regardless of level of support, will be analyzed using McNemar tests. For each of the listed primary outcomes, a series of 2X2 tables will be constructed to test changes from pre- to post- in the pertinent categories using McNemar tests. Alpha level will be adjusted to 0.025 based on Bonferroni criteria for multiple comparisons. We will also use McNemar tests to test the hypothesis that the pre- to post- level of improvement in diagnostic status, symptom severity, impairment level, coping, and academic productivity obtained during Implementation will be maintained during Sustainability among schools receiving C + C.

We would like to determine whether pre- to post- improvement in diagnostic status, symptom severity, impairment level, and academic productivity differ by support condition during the implementation phase. In addressing this research question, and for the sake of simplifying the statistical analysis, each student will be categorized as either improved or not improved based on change from pre- to post-. A category one will be assigned if a student’s diagnostic status, for example, changes either from positive to intermediate, intermediate to negative, or positive to negative. Otherwise a score of zero will be assigned. Similar coding will be used for symptom severity, coping, impairment level, and academic productivity. We will use chi-squared tests to compare the proportion of (yes/no) for each of the primary outcomes between C and C + C type of supports. To examine changes in the rate of ODRs between baseline and follow up during each school year, the number of students with at least one ODR will be defined at baseline and at the follow up and a 95% confidence interval for such changes will be constructed for each of the five years.

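### For school climate and office discipline referrals, a non-significant interaction leads the plan to report only a pooled time trend in place of the C + C versus C difference

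*Protocol article*

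**What the plan says.** Aim two (Study aims) asks whether school climate, ODRs and the Tier 2 child outcomes differ between C and C + C schools. For climate and ODRs, the Data analytic plan fits support, time (five points) and their interaction. A significant interaction is read as showing that "change in school climate and/or reduction in ODRs over time is significantly different between the two levels of support". Otherwise, "If the interaction term is statistically not significant, the changes over time for the two primary outcomes will be presented by the time effect only", and that effect is one "which represents both levels of support".

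For Tier 2, the same section adds a sustainability hypothesis: "We will also use McNemar tests to test the hypothesis that the pre- to post- level of improvement in diagnostic status", and in the other listed child outcomes, "will be maintained during Sustainability among schools receiving C + C". It does not say which observations form the pairs or what result would count as maintained. The section on child outcome measures says that diagnostic status, symptoms, coping and impairment "will be assessed at pre- and post-participation in CPP and FRIENDS".

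**The concern.** The interaction is the plan's answer to aim two for these two outcomes. A non-significant result means only that the data did not exclude equality, and with three schools per arm they may not exclude a large difference either. Under the stated rule the reader would then see one common trend and no estimate of what coaching adds. Both arms receive the programme, so the common trend cannot be separated from change that would have happened anyway. A worthwhile effect could go unreported, and so could an interval narrow enough to rule one out.

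The maintenance test has a related weakness. The null hypothesis of McNemar's test is no net change within pairs. Neither rejecting it nor failing to reject it shows that an earlier level of improvement was kept.

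**Working it through.** The article gives no power figure for the interaction, so there is none to reproduce. The calculation illustrates one contrast: the difference between arms in climate change from baseline to a single later year.

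**Inputs from the article**
- Six schools, three per arm (Methods/Design; Table 1 gives 90 staff per arm).
- 30 staff per school (School climate).
- C + C has 153 Tier 2 children (Table 1).
- Alpha 0.025 for the McNemar series (Data analytic plan).
- The only school-level variance figure is below 5%, from an evaluation of FRIENDS (Sample size justification). It does not concern staff climate scores, so using it here is an assumption.

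**Assumptions**
- Pre-post correlation 0.5, for the staff and school components alike.
- ICC from 0 to 0.05.
- Two-sided alpha 0.05 for the interaction.
- A school-level t test with 6 − 2 = 4 degrees of freedom.

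**Step 1: standard error, in SD units.** The variance of a school's mean change is 2(1 − 0.5)[(1 − ICC)/30 + ICC]. The standard error of the arm difference is √(that variance × 2/3).
- ICC 0: √(0.0333 × 2/3) = 0.149
- ICC 0.02: √(0.0527 × 2/3) = 0.187
- ICC 0.05: √(0.0817 × 2/3) = 0.233

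**Step 2: half-width and power.** The half-width is 2.776 × SE. Power comes from the noncentral t with 4 df.

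| ICC | 95% half-width | Power, 0.3 SD | Power, 0.5 SD | Non-significant at 0.5 SD |
|---|---|---|---|---|
| 0 | 0.41 | 34% | 71% | 29% |
| 0.02 | 0.52 | 24% | 53% | 47% |
| 0.05 | 0.65 | 17% | 38% | 62% |

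**Step 3: dependence on the test.** The article does not fix 4 df. With the same standard errors and a normal reference, power at 0.5 SD is 92%, 76% and 57%, so non-significance falls to 8%, 24% and 43%. If the test ignored school clustering, non-significance at ICC 0.02 and 0.05 would be about 13% and 19%. Its type I error would then be about 12% and 21% in place of 5%.

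**Step 4: the maintenance test, on its two possible readings**
- *Pre versus post within Sustainability.* Rejection shows some net change in that phase. It does not show that the Implementation level was kept.
- *Implementation versus Sustainability.* This reading needs the same children in both phases, and non-rejection would have to stand for maintenance. Suppose a net 0.125 of children lose their gain, half of the 0.25 paired difference used in the sample size section. The exact McNemar test at 0.025 with all 153 C + C children as pairs is non-significant in 31% of trials if 30% of pairs are discordant, and in 63% if 60% are. With 50 pairs the figures are 81% and 90%. The number of pairs, the discordance and the size of the loss are assumptions.

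**The case against.** The strongest defence is that the rule is narrow. It concerns how change in two outcomes is presented, and the interaction is still fitted and tested. Arm comparisons remain elsewhere: fidelity intervals by support level, a chi-squared comparison of C with C + C for the Tier 2 child outcomes during implementation, and cost-effectiveness ratios built on the between-arm difference. Diagnostic status, which drives the sample size, is outside the rule. Change across all schools is itself part of aim three, so a pooled time effect has a place. All of this stands. A reader might infer that the randomised comparison disappears from the trial, and the article does not support that. The cost-effectiveness section is only a partial answer, because it limits ratios for outcomes such as climate to comparisons showing significant improvement.

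A second objection is that the size depends on a test the article does not specify. That also stands, and Step 3 shows how far the figures move. Losses near 88% (a 0.3 SD difference at ICC 0.10) would need an ICC above the only figure in the article.

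On maintenance, three stronger readings go too far:
- *Sustainability is not tested at all.* Climate is surveyed at the end of all five years and modelled over time.
- *Children in the two phases certainly cannot be paired.* The timing of the child assessments, and the mention of later cohorts in the unmet-need analysis, suggest separate children. The article does not say so.
- *Low power makes it easier to conclude that gains were maintained.* This holds only for a between-phase test. Within Sustainability, low power makes a significant improvement harder to show.

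**Conclusion.** The point holds for the reporting of school climate and ODRs. The article states outright that the between-arm result gives way to a pooled trend when the interaction is not significant, and this conflicts with aim two. Under the assumptions listed, a real 0.5 SD difference in climate change would be lost from presentation in about 29% to 62% of trials. An interval of ±0.41 to ±0.65 SD could not support a claim that the arms share one trend. These figures are conditional and cover climate only; nothing was computed for ODRs. The objection to the rule does not depend on them, since non-significance is not evidence of equality at any power.

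The maintenance point is secondary. On either reading the McNemar test does not establish that improvement was maintained. Whether the phases contain different children is left open, so confidence in that part of the argument is lower.

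**What to change.** Replace the conditional sentence in the Data analytic plan. State that the C + C minus C difference in change in climate and ODRs will always be reported with a 95% interval that respects the six schools, whatever the interaction p-value. The pooled time effect would be given only as an additional descriptive result. This costs about two sentences and needs no new data.

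For the Tier 2 hypothesis, state which children contribute to each phase. Estimate the Sustainability minus Implementation difference in the proportion improved, with a school-clustered 95% interval, and do not conclude that improvement was maintained from a McNemar p-value. This also needs no new data, but the interval will be wide. If the 153 C + C children split evenly, at about 76 per phase, with half improved (both assumptions), the half-width is 1.96 × √(2 × 0.25/76) = 0.16 before any allowance for clustering in three schools. A formal test against a margin could therefore rarely succeed, and the result is better presented as an estimate.

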### Theoretical framework

We developed and pilot-tested the program in two K–8 schools that have the same ethnic and socio-economic breakdown as the schools participating in this study. The project was funded by the Centers for Disease Control and Prevention (CDC; RFA-CD-08-001; *Elimination of health disparities through translation research; R18*). The adaptation and testing of the interventions used in the study were organized around the first three steps of the Public Health Model (*i.e.*, Defining the problem; Identifying causes/risk factors; Developing and testing the intervention) See, [71-73] (see Figure 1). Specifically, we collected needs assessment data, assessed symptom profile and mental health service utilization of typical students in the participating schools, investigated risk and protective factors, conducted a review of EBIs for ethnically-diverse children, selected and adapted interventions based on the characteristics of the student population and specific constraints of under-resourced schools, and pilot-tested SWPBIS and EBIs for externalizing behavior problems and anxiety ([name] et. al., Development and implementation of a SWPBIS program with mental health supports in urban schools, submitted) [74]. The present study will extend this work by addressing the fourth step (Implementing the intervention/measuring effectiveness) of the Public Health Model [71]. Outcome measures for the present study were selected based on the implementation framework developed by Proctor and colleagues [75,76], including the assessment of implementation outcomes, service outcomes, and child outcomes (see Figure 1).

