### Inclusion criteria

All children will participate in Tier 1. Children in grades 4–8, who meet screening and diagnostic criteria will be included in Tier 2. The screening criterion is a score ≥1 SD on the Conduct Problems or Emotional Symptoms scales of the Strengths and Difficulties Questionnaire (SDQ), a widely-used screening instrument [78], filled out by a teacher. Children meeting screening criterion will undergo a diagnostic evaluation. Children meeting primary diagnosis of ODD, CD, GAD, SAD, or SP (based on a parent structured interview [79] and a symptom severity scale [80] filled out by an independent rater) at Intermediate or Positive level will be eligible for participation. Children with comorbid (secondary) conditions will be included.

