### Exclusion criteria

There are no exclusion criteria for Tier 1. Children with a Special Education classification of Intellectual Disability, as well as those who are not able to communicate in English, do not have a principal diagnosis of ODD, CD, SAD, GAD or SP or are not at risk for one of those disorders, have an accumulated absenteeism record of ≥33% for the current year, or have a history of psychotic or autistic spectrum disorders, will be excluded from Tier 2.

### Linkage between Tier 1 and Tier 2

The leadership teams and the counselors will manage the SWPBIS program. They will be in charge of identifying, eliminating, or consolidating existing school-wide interventions that could overlap or interfere with the implementation of SWPBIS. Existing behavioral health services for individual students (*e.g.*, wrap-around services) will be maintained because they will not interfere with SWPBIS. The leadership teams in each school will develop all interventions for Tier 1 while receiving C or C + C. A subcommittee within the leadership team composed of a counselor and an administrator will be in charge of identifying and referring children for participation in Tier 2. Following methods used in other studies [81] each teacher will be asked to rank the children in their classroom from least to most difficulty with externalizing behavior or anxiety and then to refer the top three children with externalizing behavior problems and top three children with excessive anxiety for possible participation in Tier 2. Decisions as to the appropriateness of referrals to Tier 2 will be based on data gathered via teacher ratings on the SDQ [78] and a web-based software system [82] for collecting and summarizing office discipline referrals.

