### Sample size justification and statistical power

Sample size estimation was based on addressing the primary outcome, the participants’ diagnostic status (aim two). The statistical analysis will be McNemar tests for two correlated proportions (pre/post) between two groups. With a sample size of 300 students, the statistical test achieves 92% power to detect an odds ratio of three using a two-sided McNemar test with a significance level (α ) of 0.01. The odds ratio is equivalent to a difference between two paired proportions of 0.25, which occurs, for example, when the proportion among students diagnosed with a Positive anxiety/externalizing disorder at pre and improved to Intermediate at post (cell 1,2 in the 2X2 McNemar table) is 0.425 and the proportion among students diagnosed without Positive anxiety/externalizing disorder who became either Intermediate or Positive at post (cell 2,1 in the 2X2 McNemar table) is 0.175. Therefore, the proportion of discordant pairs is 0.60. We adjusted α level to 0.01 to account for the multiple 2X2 McNemar testing. We need to recruit six schools, grades four to eight,to be able to enroll 300 evaluable students who meet inclusion criteria. We assumed that the observed changes in students’ diagnostic status within schools are independent based on an evaluation of the FRIENDS program, in which ‘schools’ level accounted for less than 5% of the total variance across dependent measures.

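### Tier 2 entry depends on the same parent interview that measures the primary outcome, and every child gets the groups, so the pooled pre-post McNemar test leans towards improvement and cannot show a programme effect

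*Protocol article*

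**What the plan says.** **Entry.** Under Inclusion criteria, a child needs a primary diagnosis of one of five disorders, "based on a parent structured interview [79] and a symptom severity scale [80] filled out by an independent rater", and only those "at Intermediate or Positive level will be eligible for participation". Exclusion criteria repeat the bar: children who "do not have a principal diagnosis of ODD, CD, SAD, GAD or SP or are not at risk for one of those disorders" are kept out. Before the interview, teachers rank their pupils and "refer the top three children with externalizing behavior problems and top three children with excessive anxiety" (Linkage between Tier 1 and Tier 2), and the teacher SDQ must be at least 1 SD.

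**Outcome.** Child outcome measures for at risk/high risk children takes diagnostic status, pre and post, from a parent structured interview cited to the same reference (79). It has three levels per disorder: Positive, Intermediate, Negative. No second baseline interview after eligibility is described.

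**Analysis.** Changes from pre to post "during Implementation across all schools, regardless of level of support, will be analyzed using McNemar tests", with alpha 0.025 (Data analytic plan). The next paragraph of that section plans a chi-squared comparison of improved versus not improved between C and C + C.

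**Sizing.** "Sample size estimation was based on addressing the primary outcome", named as diagnostic status, using a two-sided McNemar test with 300 students, alpha 0.01, an improving cell of 0.425, a worsening cell of 0.175 and 92% power.

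**The concern.** McNemar's null is that as many children worsen as improve. That null is informative about treatment only if, without treatment, moves in the two directions would balance. Here the sample is cut off from below on the pre value of the outcome itself. Some children qualify because the interview caught them at a high point, and on repeat they tend to fall back. The children who would have balanced them, low at pre and higher at post, were not admitted. Ordinary remission over the course of the groups adds to this. Both arms get the groups, so nothing in the pooled test separates these effects from the programme.

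At stake is what the trial can conclude from the test that carries its primary outcome and its sample size. The Theoretical framework places the study at the step "Implementing the intervention/measuring effectiveness", and Challenges and limitations mentions neither regression to the mean, nor natural course, nor the lack of untreated children. A reader of a significant pooled result would have no warning.

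**Working it through.** **1. The plan's own power figure.** Inputs (Sample size justification and statistical power): cells 0.425 and 0.175, so d = 0.25 and discordant share pd = 0.60; n = 300; two-sided alpha 0.01, z = 2.576.

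Power = Φ[(d√n − z√pd) / √(pd − d²)] = Φ[(4.330 − 1.995) / 0.733] = Φ(3.18) = 99.9%. The exact calculation also gives 99.9%.

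The stated 92% is not reproduced at n = 300. It appears at n = 150, about one arm: Φ[(3.062 − 1.995) / 0.733] = Φ(1.46) = 92.7%, or 91.7% exact. The cells give an odds ratio of 0.425/0.175 = 2.43, not 3. Alpha is 0.01 here and 0.025 in the Data analytic plan. These are separate matters. For this point, a pre-post test within one arm would be just as uncontrolled.

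**2. The worsening cell.** The 0.175 cell is described as children without a Positive diagnosis at pre who become Intermediate or Positive. Moving up to Intermediate requires a Negative start, which the entry rules bar for the qualifying disorder. Only Intermediate to Positive remains possible.

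**3. Negative versus not-Negative table, qualifying disorder.** The worsening cell is 0 by design. With k improvers the exact two-sided p is 2 × 0.5^k:
- k = 7: 0.0156, below 0.025
- k = 8: 0.0078, below 0.01

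Eight of 300 is 2.7%. As an illustration only, the section GCBT for externalizing and anxiety problems cites a trial in which 6% of wait-list children were diagnosis-free at the end of 10 weeks. Six per cent of 300 is 18. If each child had that chance, P(8 or more of 300) = 99.8%. That population and endpoint may differ from this trial's.

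**4. Positive versus not-Positive table.** Assume a latent severity with the same distribution at pre and post, retest correlation r and no true change. Let c1 be the entry cut, c2 the Positive cut and q the share of interviewed children who qualify.

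Improved = P(z1 ≥ c2, z2 < c2)/q. Worsened = P(c1 ≤ z1 < c2, z2 ≥ c2)/q.

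By symmetry, P(z1 ≥ c2, z2 < c2) = P(z1 < c2, z2 ≥ c2), so

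improved − worsened = P(z1 < c1, z2 ≥ c2)/q.

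The excess of improvers is exactly the group that would have gone from Negative to Positive and was never admitted. It cannot be negative, so the direction is fixed. Its size is not.

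Exact McNemar rejection rates with no programme effect, n = 300, alpha 0.01. The documents give neither q, r nor the Positive cut; all are assumed.

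| Assumed entry | r = 0.6 | 0.7 | 0.8 | 0.9 |
|---|---|---|---|---|
| +1 SD of an unscreened normal, Positive at +1.25 SD | 100% | 100% | 99.9% | 77% |
| same, Positive at +1.5 SD | 99% | 92% | 51% | 6% |
| same, Positive at +2 SD | 19% | 6% | 1.5% | 0.6% |
| 30% of interviewed qualify, half Positive | 96% | 78% | 35% | 4% |
| 50% qualify, half Positive | 50% | 23% | 6% | 1% |
| 70% qualify, half Positive | 8% | 3% | 1% | 0.7% |
| 90% qualify, half Positive | 1% | 0.8% | 0.7% | 0.7% |

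Example (50% qualify, r = 0.7): improved 0.199, worsened 0.135, excess 0.064.

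Under the same model with 30%, 50% or 70% qualifying, the Negative versus not-Negative table rejects in at least 99.8% of null trials for r from 0.5 to 0.95. The lowest scenario tried (90% qualify, r = 0.95) gives 46%.

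The model leaves out natural remission and the teacher-based screens, both of which would add to the bias.

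**The case against.** The strongest reply is that the randomised comparison is intact. The Data analytic plan goes on to compare improvement between C and C + C, the second study aim is that between-arm question, and selection acts alike in both arms. The article nowhere says that a significant pooled test would be read as proof that the programme works; the effectiveness wording in the Theoretical framework is the name of a step in a public health model. Reporting within-group change beside a randomised contrast is common, and the article condenses a fuller plan.

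Most of this stands. A reader might infer that pooling throws away the randomised contrast; it does not, because that contrast is planned separately. A reader might also infer that a significant pooled result is nearly assured. The documents do not support that either. The empty-cell argument needs a Negative versus not-Negative table, which the protocol never specifies. For the cut it does illustrate, the false-significance rate falls to about nominal if the interview is very reliable or if most interviewed children qualify. A high qualifying share is plausible after referral and SDQ screening. Those earlier screens also use a different informant from the outcome, so only the interview step selects directly on the pre value.

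What the reply does not meet is that the uncontrolled test, with a set alpha, is the one named for the primary outcome and used for sizing. Test, pooling and primary status are all fixed in this text, so they are not details left to a fuller plan.

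**Conclusion.** The concern holds for the pooled pre-post test. Entry on the outcome interview, with all children treated, biases it towards improvement, and it cannot attribute change to the programme. With an unchanged severity distribution the direction is certain. The size is not: false significance is high for a Negative versus not-Negative table (8 improvers of 300 suffice), and anywhere from near 100% to about nominal for Positive versus not-Positive, depending on assumed retest correlation and cut-offs.

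The argument is strongest for diagnostic status. It is weaker for coping and academic productivity, which are in the same McNemar family but are not entry criteria. It does not touch the C + C versus C comparison, which is not biased in this way in expectation.

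**What to change.** **Data analytic plan.** Report the pooled pre-post changes descriptively, as proportions with confidence intervals, without a significance test as evidence of effect. State that programme effect cannot be separated there from selection and natural course.

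**Sample size justification and statistical power.** Remove primary status from the pooled change. Make the already planned C + C versus C comparison the basis for Tier 2 effect conclusions, using post status adjusted for pre status and accounting for school clustering. Reconcile the worsening cell with the entry rules.

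**State the precision of that contrast with six schools.** As an illustration, take the protocol's upper figure of 5% of variance at school level as the intraclass correlation, with 51 children per school. The design effect is 1 + 50 × 0.05 = 3.5, so 306 children count as about 87, or 44 per arm. For proportions near 0.5 the standard error of the difference is √(0.5/43.7) = 0.107. The 95% half-width is about 0.21 with a normal quantile, or 0.30 with t on 6 − 2 = 4 degrees of freedom. A smaller correlation, or gain from adjusting for pre status, would narrow this.

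**Cost.** Wording and a re-ranking of analyses on data already to be collected. The trial gives up its pre-post significance claim, and the stated 92% power no longer applies to the main Tier 2 comparison.

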### Data analytic plan

The statistical analyses for each of the study aims are described below: in addressing aim one, mean fidelity and its 95% confidence intervals for Tier 1 will be calculated using 20 randomly selected participants from each of the six schools during years three, four, and five (120 total per year). The 95% confidence intervals will be presented by C & C + C for all schools combined and for each school. Content and process fidelity data for Tier 2 will be obtained by scoring 14 video recorded sessions per each of the treatment groups. Perception of School Climate (aim two) during year one will be surveyed by a randomly selected sample of teachers, support staff and administrators from each participant school. The randomly selected sample will consist of similar proportion of teachers, support staff and administrators within each school. The questionnaire [101] will be completed at the end of years one, two, three, four, and five. This 31-item, 5-point Likert type scale checklist has four factors. Each factor’s total score will be analyzed separately. School personnel no longer present in the school during subsequent years will be replaced.

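### The pre-post McNemar tests carry a Bonferroni alpha of 0.025 in the analysis plan but 0.01 in the sample size section, and only 0.01 fits the five outcomes listed; the label for the primary outcome also shifts

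*Protocol article*

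**What the plan says.** The Data analytic plan lists five child outcomes for analysis from pre to post across all schools, whatever the level of support: diagnostic status, symptom severity, impairment level, coping skills and academic productivity. It refers to them as the listed primary outcomes, says that several 2x2 tables will be built for each and tested by McNemar, and continues: "Alpha level will be adjusted to 0.025 based on Bonferroni criteria for multiple comparisons".

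The section Sample size justification and statistical power describes the same kind of test, two-sided, and gives another figure: "We adjusted α level to 0.01 to account for the multiple 2X2 McNemar testing".

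The word primary is used in three ways:

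- Sample size section: "Sample size estimation was based on addressing the primary outcome", which it identifies as diagnostic status (one outcome).
- Data analytic plan, McNemar paragraph: the five child outcomes.
- Data analytic plan, mixed model and GEE paragraph: "the changes over time for the two primary outcomes will be presented by the time effect only". From the sentence before it, these two are school climate and office discipline referrals (ODRs).

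**The concern.** Both sections present their alpha as a multiplicity correction for McNemar tests on 2x2 tables, so they should give the same number. A result with p = 0.015, for example, passes in one section and fails in the other. The figure in the analysis plan is also the one that does not match the number of outcomes it is attached to.

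The shifting label makes this worse. How far alpha must be divided depends on which outcomes form the family, and the article does not settle whether the confirmatory Tier 2 outcome is diagnostic status alone or all five child outcomes.

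**Working it through.** **Inputs.** Five child outcomes and alpha 0.025 (Data analytic plan). Alpha 0.01, two-sided, n = 300, discordant cells 0.425 and 0.175, stated power 92% (sample size section). Assumption: the overall level being protected is 5%. The article does not state it, but both figures are simple fractions of it.

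**1. Where each alpha comes from.**
- 0.05/5 = 0.01, a family of five.
- 0.05/2 = 0.025, a family of two.

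The list beside 0.025 has five members, so 0.01 fits that list and 0.025 does not.

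**2. Family-wise error, one test per outcome.** The Bonferroni bound is k × alpha; under independence the error is 1 − (1 − alpha)^k.

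| Tests k | Alpha | Bound | If independent |
|---|---|---|---|
| 2 | 0.025 | 0.050 | 1 − 0.975² = 0.049 |
| 5 | 0.025 | 0.125 | 1 − 0.975⁵ = 0.119 |
| 5 | 0.01 | 0.050 | 1 − 0.99⁵ = 0.049 |

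**3. Sensitivity to the number of tables.** The plan speaks of several tables per outcome, and diagnostic status has three levels (Child outcome measures for at risk/high risk children). If, as an assumption, each outcome gave three tests, there would be 15. The bound would then be 15 × 0.01 = 0.15 even at the stricter alpha, and Bonferroni would need 0.05/15 = 0.0033. The 5% bound at 0.01 therefore holds only with one test per outcome.

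**4. Which alpha was used for sizing.** The normal approximation to McNemar power is Φ[(d√n − z√p_d)/√(p_d − d²)], with d = 0.425 − 0.175 = 0.25, p_d = 0.60 and z the two-sided critical value.
- n = 300, alpha 0.01 (z = 2.576): (4.330 − 1.995)/0.733 = 3.19, power 99.9%. The stated 92% is not reproduced.
- n = 150, alpha 0.01: (3.062 − 1.995)/0.733 = 1.46, power 92.7% (exact 91.7%). This matches the stated 92%.
- n = 150, alpha 0.025 (z = 2.241): (3.062 − 1.736)/0.733 = 1.81, power 96.5% (exact 95.8%). This does not match.

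The stated power thus agrees with alpha 0.01 and with about half the stated sample. The mismatch in n is a separate matter. What counts here is that the planning calculation used 0.01, as the text says.

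**The case against.** **The two alphas might serve different purposes.** The sample size section specifies the test as two-sided ("using a two-sided McNemar test with a significance level"), and the analysis plan attributes 0.025 to Bonferroni, so 0.025 cannot be taken as a one-sided restatement. It might have been derived from the two Tier 1 outcomes. But the sentence sits in the McNemar paragraph, those two are analysed by mixed model or GEE, and climate has four factors for which each "total score will be analyzed separately". It might stand for two comparisons per outcome, but the text does not say so, and the other section would still give 0.01 for the same testing.

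**An analysis plan that is not shown may settle it.** It could choose one figure, but the article itself fixes two, and a plan faithful to one section would contradict the other. This objection does dispose of two stronger readings. A reader might infer that the between-arm chi-squared tests are left uncorrected, or that the choice of outcome and threshold stays open until the data are seen. A condensed article may leave such matters to the analysis plan, so neither is supported.

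**The three uses of primary are not all rivals.** This stands in part. A reader might infer three competing definitions. Climate and ODRs, however, can be read as a separate Tier 1 family, since the article separates the tiers throughout. The clear conflict is within Tier 2: one primary outcome against five.

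**Family-wise error is not lost everywhere.** This also stands. A reader might infer that the plan fails to control it at all. At 0.01 with one test per outcome, the five pre-post tests are held at 5%. The failure belongs to the 0.025 statement.

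**The stakes are limited.** These are uncontrolled pre-post tests across all schools, not the randomized comparison, and sizing used the stricter alpha. Both points are correct and bound the consequence.

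**Conclusion.** The contradiction is real and needs correcting. Two thresholds are given for the same McNemar testing, and 0.025 does not fit the five outcomes to which it is applied. Taken as written, it allows a family-wise error of up to 12.5% (11.9% if the tests are independent) against an assumed 5%, with one test per outcome. In practice the conflict decides the status of any pre-post result with p between 0.01 and 0.025.

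The Tier 2 primary outcome is also labelled inconsistently, as diagnostic status alone or as all five child outcomes. The reference to two primary outcomes should be clarified, but it is not necessarily a third competing definition. The sample size is not affected by the conflict in alpha.

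**What to change.** - In the Data analytic plan, replace 0.025 with the 0.01 used for sizing, and apply it to one pre-specified 2x2 test for each of the five child outcomes. If more than one table per outcome is to be tested, divide 0.05 by the actual number of tests and state that number in both sections.
- Use one label throughout: diagnostic status as the primary Tier 2 outcome, as in the sample size section, and the other four child outcomes as secondary. A single primary outcome would not by itself require division by five. Keeping 0.01 for all five matches the planning calculation and covers the whole set.
- In the mixed model and GEE paragraph, identify climate and ODRs as the Tier 1 outcomes, so that the reference to two primary outcomes cannot be read as a rival to diagnostic status.

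The cost is wording in three places and a slightly stricter threshold for the pre-post tests. For diagnostic status, under the article's own cells and its assumption of independence within schools, moving from 0.025 to 0.01 lowers power from 96.5% to 92.7% at n = 150, and leaves it above 99.9% at n = 300 (normal approximation). No change in sample size is needed.
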